### Statistical analysis

The main analysis will compare HADS scores of all patients at t4 in arm one versus arm two using t-tests. Subsequently, only patients highly distressed at baseline in the two groups will be compared regarding their HADS score at t4. Because of the limited number of departments, complete control for confounding cannot be guaranteed despite randomization; therefore the following variables will be subsequently adjusted for in a mixed-model analysis: sex, age, stage of disease and baseline distress. The analyses will be done as according to the intention to treat principle. No interim analyses are planned.

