## Methods/Design

### Design

Experience from previous studies teaches us that investigating complex behavioral interventions with ‘simple’ randomized trials can create misleading results. If, for example, students in a class are individually randomized to either be trained to stop smoking or not, the outcome ‘change in frequency of smoking’ will not entirely be related to the training itself. Students will talk to each other in the class, and, especially if one of the informal leaders (‘opinion maker’) in this class stops smoking, this will affect other students and they will be more likely to stop smoking as well. From a public health perspective, this is a most welcome effect. Technically speaking, however, this is an undesired effect, because it will blur the effects of the intervention; students in the control group will show an effect as well. In other words, individual randomization for the purpose of testing behavioral interventions in larger groups will likely result in an underestimation of the treatment effect. An alternative is the use of cluster randomization [17]. Here, clusters of individuals are randomized rather than individuals themselves, for example wards or clinics.

In our cluster randomized study, we randomized wards. Two parallel groups are compared and the intervention is expected to be superior to the control arm. The setting of this study is an academic hospital: University Medical Center Leipzig in Leipzig, Germany. Informed consent is obtained from each study participant after admittance to the ward, before the baseline assessment.

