### Sample size

At the University Medical Center Leipzig, 2,000 patients with malignant diseases are treated per year according to the local cancer registry. Of those, about 350 are ineligible for the study because of age or because they are treated at a ward that is not participating in this study, leaving 1,650 eligible patients per year and 137 per month. Thus, about 1,200 patients can be approached initially. Assuming that 20% of patients will decline participation at t1, this leaves about 1,000 patients participating at baseline. Based on previous experience from a large epidemiological study with cancer patients at the University Medical Center Leipzig [22], we assumed that 20% of the patients would drop out during the follow-up period due to death or withdrawal from the study, leaving 800 patients at t4.

Cluster randomized trials must take into account the within- and between-cluster variation by increasing the sample size [30]. The between-cluster-variation coefficient could only be approximately estimated because of a lack of data in the literature. We therefore used the recommendation of Hayes and Bennett [30] and assumed k = 0.2. We further assumed an equal cluster size. In our trial, 13 clusters are included and randomized. The low number of clusters was considered in the sample size calculation with a specific formula (t-distribution). Data from a previous large study in the same hospital [22] suggests that the average HADS score in cancer patients is 13, with a standard deviation of 7. This is the expected mean HADS score in the control arm at t4. With 13 clusters, k = 0.2, α = 0.05, a power of 80%, and n = 400 per arm, a delta in HADS scores of 5.5 can be identified. If k should be k = 0.1, a difference of 4.1 can be detected.

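### Wards were randomised, but the main analysis as written is a patient-level t-test: type I error is about 26% to 50-52% under the protocol's own k values, not 5%

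*Protocol article*

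**What the plan says.** The protocol article is clear about the unit of randomisation. Under Design: "In our cluster randomized study, we randomized wards".

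The Sample size section draws the consequence: "Cluster randomized trials must take into account the within- and between-cluster variation by increasing the sample size". It gives the number of clusters, "In our trial, 13 clusters are included and randomized", and uses a t-distribution because they are few. On ward size it says "We further assumed an equal cluster size". The planning value for between-ward variation is k = 0.2, with a more favourable alternative: "If k should be k = 0.1, a difference of 4.1 can be detected".

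The Statistical analysis section then fixes the deciding test: "The main analysis will compare HADS scores of all patients at t4 in arm one versus arm two using t-tests". A second comparison is restricted to patients with high distress at baseline. A further model follows: "therefore the following variables will be subsequently adjusted for in a mixed-model analysis: sex, age, stage of disease and baseline distress". The reason given for it is that, with few departments, randomisation may not balance confounders. The section mentions no ward means, ward effect or variance correction.

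The section on reducing confounding and bias adds that the randomisation was stratified by each department's past use of the consultation liaison service.

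**The concern.** Patients on one ward share doctors, case mix and routines, so their HADS scores are correlated. When whole wards are allocated, the arm difference varies by chance with the ward effects as well as with the patients. A t-test on individual scores counts only the patient variation. Its standard error is too small by the square root of the design effect, and its p-values and confidence intervals are invalid.

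This test decides the primary endpoint. If it is run as written, ordinary differences between wards can be reported as an effect of stepped care. The article's Discussion hopes that the model, if proven effective, will be taken up in other hospitals, so a false positive would have consequences.

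**Working it through.** **The plan's own figures.** The article gives detectable differences of 5.5 (k = 0.2) and 4.1 (k = 0.1). I tried the usual formula for unmatched clusters, d² = (t₀.₉₇₅ + t₀.₈₀)² × [2·SD²/m + k²(μ₀² + μ₁²)]/c, with 11 df, c = 6.5 wards per arm, m = 61.5, SD = 7, μ₀ = 13 and μ₁ = 13 − d. It gives about 4.1 and 2.5, or 4.7 and 2.7 if the between-ward SD is the same in both arms. No variant tried returned both printed values. That is a separate matter, and nothing below uses 5.5 or 4.1.

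**Inputs, all from the Sample size section:** 800 patients at t4, 13 wards of equal size, mean HADS 13, SD 7, k = 0.2 or 0.1, alpha 0.05. Assumed because the article does not say: a two-sided test, a split of 6 versus 7 wards (6.5 per arm in the formulas), and whether SD 7 is the within-ward or the total SD (both are shown).

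**Steps**

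1. Ward size: m = 800/13 = 61.5.
2. Between-ward SD = k × 13, which is 1.3 at k = 0.1 and 2.6 at k = 0.2.
3. ICC = SDb²/(SDb² + 49) if 7 is the within-ward SD, or SDb²/49 if it is the total SD.
4. Design effect DE = 1 + (m − 1) × ICC.
5. True two-sided type I error of the patient-level test = 2 × [1 − Φ(1.96/√DE)].

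| k | SD 7 is | ICC | DE | 1.96/√DE | Type I error |
|---|---|---|---|---|---|
| 0.1 | within | 1.69/50.69 = 0.033 | 3.02 | 1.13 | 26% |
| 0.1 | total | 1.69/49 = 0.034 | 3.09 | 1.12 | 26% |
| 0.2 | within | 6.76/55.76 = 0.121 | 8.34 | 0.68 | 50% |
| 0.2 | total | 6.76/49 = 0.138 | 9.35 | 0.64 | 52% |

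**Simulation check.** With 20,000 trials per setting and 6 versus 7 equal wards, the patient-level t-test rejected in 26-27% of null trials at k = 0.1 and in 50-53% at k = 0.2. A t-test on the 13 ward means with 11 df rejected in about 5% in the same settings.

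**Interval width (SD 7 as total).** The patient-level standard error is 7 × √(2/400) = 0.495, so the 95% half-width is 1.96 × 0.495 = 0.97 HADS points. The correct standard error is 0.495 × √3.09 = 0.87 at k = 0.1 and 0.495 × √9.35 = 1.51 at k = 0.2. With t = 2.20 on 11 df, the half-widths are about 1.9 and 3.3 points.

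**Sensitivity**

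- Smaller k: k = 0.05 gives 11%.
- Stratification: if it removed half of the between-ward variance (an assumption), the rates would be about 17% at k = 0.1 and 39% at k = 0.2.
- Unequal wards: at k = 0.2, a coefficient of variation of ward size of 0.57 gives 54-57%, and 0.92 gives 59-61%. The article gives no ward sizes and assumes them equal.

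**The case against.** **The unit of analysis is not named.** The reference to all patients partly serves as a contrast to the subgroup in the next sentence. The sample size rests on a cluster formula with a t-distribution, which would fit a t-test on ward means. The article is condensed, and an analysis plan that is not shown could say so. This is fair, and it is why the point concerns the test as written. Still, the article states its primary test, and comparing the scores of all patients is most plainly a patient-level comparison. If ward means were intended, the sentence still needs correcting.

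**A mixed model is planned.** In a ward-randomised trial such a model would ordinarily carry a ward effect, so a reader might infer too much in saying that the plan ignores clustering altogether. The documents do not support going that far. But the model is not the main analysis, its stated purpose is covariate adjustment, and ward is not named in it. It does not protect the deciding test.

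**The size is uncertain.** The article itself says that k could be estimated only approximately, and the stratified randomisation may remove some between-ward variance. Both are right, and the size has to be stated as conditional. None of the lower figures calculated above comes near 5%.

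**Two stronger readings do not stand.** A reader might take k = 0.2 as an intraclass correlation and arrive at about 59% (DE = 1 + 60.5 × 0.2 = 13.1). The article describes k as a coefficient of between-cluster variation, which does not support that reading. With equal wards, 60% would need k of about 0.25 to 0.30. A reader might also set the difference detectable by a naive test, about 1.4 points (2.80 × 0.495), against the stated 5.5. Since 5.5 does not follow from the stated inputs, it is not a sound benchmark.

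**Conclusion.** The concern holds as a mismatch between the design and the main test as written. Wards are randomised and the sample size allows for them, but the deciding t-test does not, and the later mixed model does not repair this.

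The type I error is about 26% at k = 0.1 and 50-52% at k = 0.2, against a nominal 5%. This rests on the article's mean, SD, k and equal ward size, and on an assumed two-sided alpha of 0.05. It is conditional on those values: strongly unequal wards would raise it, and a smaller k or effective stratification would lower it. A figure near 60% is not supported without an added assumption. The point must be fixed, because it affects the validity of the primary result.

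**What to change.** Rewrite the main analysis so that it respects the randomised unit. Either of these is sufficient:

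- a t-test comparing the 13 ward means of t4 HADS between arms, with 11 df, or fewer if the randomisation strata are included (their number is not stated in the article); or
- a linear mixed model for t4 HADS with a random ward intercept and small-sample degrees of freedom (Satterthwaite or Kenward-Roger).

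Apply the same approach to the comparison of highly distressed patients, and name ward as a random effect in the covariate-adjusted mixed model. Remove the patient-level t-test as the deciding analysis. If ward means were intended all along, say so explicitly.

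The cost is one paragraph of wording, with no additional patients or data. The confidence intervals will be wider than those of the patient-level test, which correctly reflects what 13 wards can show.

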### Data collection

The primary endpoint mental health is ascertained with the Hospital Anxiety and Depression Scale (HADS) [21]. HADS identifies depressed patients with a sensitivity of 0.96 [22]. Social problems are measured with the European Organisation for Research and Treatment of Cancer Quality of Life Questionnaire Core Instrument (EORTC QLQ-C30), using the social functioning and role functioning scales [23]. Satisfaction with care is measured with the Quality of Care from the Patients Perspective questionnaire (QPP) [24], psychiatric comorbidity is measured with the Structured Clinical Interview (SCID) [25]), and the utilization of medical care is measured with the questionnaire used in the German Federal Health Survey [26]. Clinical data are obtained from the medical records. The provision of CL services and/or social services is ascertained from the hospital information system.

The patients are interviewed at the beginning (t1) and the end (t2) of the hospital stay, three months after baseline (t3) and six months after baseline (t4). At t1 and t2, data collection is done electronically with the help of tablet computers. At t3 and t4, it will be done via phone or face-to-face, depending on the patient’s preference. For patients who prefer paper-based data collection, this is possible as well. The equivalence of both methods is well documented [27, 28, 16]. The Computer-Based Health Evaluation System (CHES) software (Evaluation Software Development, Innsbruck, Austria) is employed for electronic data capture [29]. Electronic data capture ensures that no missing data are in the data set unless the patient quits the study. Study nurses with an academic psychology education contact the patients, inform them about the study, obtain written informed consent and perform data collection. Patients in the control wards undergo the same assessments as patients in the experimental wards.

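### The main t-test of t4 HADS is not adjusted for baseline, although the plan's own reason for adjusting applies to it; the cost is mainly avoidable variance

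*Protocol article*

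**What the plan says.** The Statistical analysis section of the protocol article fixes the primary comparison: "The main analysis will compare HADS scores of all patients at t4 in arm one versus arm two using t-tests". No covariate is named for it. The section then gives a reservation, "Because of the limited number of departments, complete control for confounding cannot be guaranteed despite randomization", and the remedy for it: "therefore the following variables will be subsequently adjusted for in a mixed-model analysis: sex, age, stage of disease and baseline distress". The adjusted model is therefore planned, but as a follow-on.

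The baseline data are planned for both arms. Under Data collection, "The patients are interviewed at the beginning (t1) and the end (t2) of the hospital stay", and "Patients in the control wards undergo the same assessments as patients in the experimental wards". HADS is named there as the instrument for the primary endpoint. The article does not state outright that the baseline distress in the model is the t1 HADS score, or that t1 HADS is taken before results are fed back to the doctor.

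**The concern.** The reason given for adjusting is that few units were randomised. That is a property of the design, so it holds for the t-test as much as for the mixed model. The plan names a weakness of its primary comparison and addresses it only in a later analysis. If the two results differ, the one labelled main is the one that the plan itself regards as less protected.

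The wards belong to organ-specific departments (urology, neurosurgery, gynecology and others, under Eligibility), so mean distress may well differ between wards. With 13 wards, the arms can differ at baseline by chance. Part of such a difference would reappear at t4 and add noise that the baseline score could remove. At stake are the precision of the primary estimate and the risk of two competing answers.

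**Working it through.** **Inputs from the Sample size section.** The article says that "the average HADS score in cancer patients is 13, with a standard deviation of 7" and, of that mean, "This is the expected mean HADS score in the control arm at t4". It also gives k = 0.2 with 0.1 as the alternative, 13 clusters, and 400 patients per arm at t4. The between-ward SD is k × 13, which is 2.6 or 1.3.

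**Assumptions that the article does not give.**
- The same mean, SD and k hold at baseline.
- Wards split 6/7, with equal size 400/6.5 = 61.5.
- SD 7 is the within-ward SD, and stratification brings no benefit.
- The baseline–t4 correlation r is 0.5 to 0.7 with equal SDs, so that the slope equals r.

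**The plan's own figures.** The plan gives no figure for baseline imbalance. The nearest figures are the detectable differences of 5.5 (k = 0.2) and 4.1 (k = 0.1). With the SEs from step 1 and t quantiles on 11 df, (2.201 + 0.876) × 1.53 = 4.7 and 3.077 × 0.88 = 2.7. These do not reproduce the stated values. That is a separate question, so the gain below is given as a percentage of the SE.

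**Step 1: chance imbalance in mean baseline HADS.** SE = √[(SD_ward² + 49/61.5)(1/6 + 1/7)].
- k = 0.2: √[(6.76 + 0.797) × 0.3095] = 1.53. The 95% limits are ±1.96 × 1.53 = ±3.0, and the mean absolute difference is 0.798 × 1.53 = 1.2.
- k = 0.1: √[(1.69 + 0.797) × 0.3095] = 0.88. The limits are ±1.7, and the mean absolute difference is 0.7.
- With 500 per arm, as expected at baseline, the limits are ±2.96 and ±1.66.

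**Step 2: carry-over to t4.** About r times the baseline difference is expected to reappear.
- From 3.0 points: 0.5 × 3.0 = 1.5 to 0.7 × 3.0 = 2.1.
- From 1.7 points: 0.5 × 1.7 = 0.85 (about 0.9) to 0.7 × 1.7 = 1.2.

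**Step 3: what adjustment does to the SE.** Let V = SD_ward² + 0.797. The ranges run from r = 0.5 to r = 0.7.

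| Case | SE multiplier | k = 0.2 | k = 0.1 |
|---|---|---|---|
| A. r holds at ward and patient level | √(1 − r²) | 0.87 to 0.71 | 0.87 to 0.71 |
| B. Baseline explains only within-ward variance, and wards do not differ at baseline | √[(SD_ward² + (1 − r²) × 0.797)/V] | 0.99 to 0.97 | 0.96 to 0.92 |
| C. Ward means differ at baseline but are unrelated to those at t4; one patient-level slope | √[(SD_ward²(1 + r²) + (1 − r²) × 0.797)/V] | 1.09 to 1.18 | 1.04 to 1.08 |

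Case A cuts the SE by 13–29%: from 1.53 to 1.32–1.09 at k = 0.2, and from 0.88 to 0.76–0.63 at k = 0.1. With 10 df, the recomputed detectable difference falls from 4.7 to 4.1–3.4 and from 2.7 to 2.4–1.9. Case B gains 1–8%. Case C loses 9–18% at k = 0.2 and 4–8% at k = 0.1. The loss arises because, with about 61 patients per ward, the slope is set almost wholly within wards and is then applied to ward differences that it does not predict.

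**The case against.** The strongest reply is that the adjusted model is already prespecified, so the dispute is only over which result is called main. It is also true that randomisation was stratified by past use of the consultation liaison service, expressly to reduce baseline differences, and that the imbalance figures apply t4 inputs to baseline. All of this stands. It makes the limits in step 1 illustrative and probably at the upper end. It does not explain why the remedy for a recognised weakness should stay out of the primary test, and the plan still calls control incomplete despite randomisation.

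Three stronger readings are tempting, and the documents do not support them.
- *A reader might infer that up to 3 points passes straight into the primary result.* Three points is a 95% limit at the larger k, exceeded about 5% of the time, and not a maximum. Full carry-over would need r = 1, and the article gives no correlation.
- *A reader might infer that the main test is biased.* Chance imbalance between randomised wards is variance, and a ward-aware test carries it in its standard error. It misleads the test mainly if the t-test ignores wards, which is a separate question.
- *A reader might infer that adjustment cannot lose.* Case C shows that it can. That case is unlikely, but no figure in the article excludes it.

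The t1 score is also not documented as a clean covariate. Consent and t1 come after ward randomisation, and each study nurse works in one arm only, so t1 scores could differ by arm through recruitment or measurement. The article does not show that they do.

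**Conclusion.** The point holds as a matter of efficiency and coherence. The main test omits a baseline measure that is planned for both arms and that the plan itself says is needed because so few departments are randomised. On the stated assumptions, an imbalance at the 95% limits (1.7 to 3.0 points) would move the t4 difference by about 0.9 to 2.1 points, and the typical imbalance is smaller, at 0.7 to 1.2 points. The likely benefit of adjusting is an SE lower by 13–29%. That rests on a correlation of 0.5 to 0.7 at ward level as well as patient level, which the article neither gives nor rules out. The gain may be as small as 1%, and a loss is possible in an unlikely case. The change should be made because it is nearly free, and not because the present test is invalid for lack of a covariate.

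**What to change.** Make the mixed model that is already planned the single primary analysis of t4 HADS. Specify a ward random effect, t1 HADS as a continuous covariate, and sex, age and stage as listed. State that t1 HADS is the baseline distress measure and that it is taken before any feedback to the doctor. Use small-sample degrees of freedom suited to 13 wards (for example Kenward–Roger or Satterthwaite). Keep an unadjusted, ward-aware comparison of t4 HADS as a sensitivity analysis.

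The cost is wording only, since the assessment and the model are already planned. If one degree of freedom is lost at ward level (11 to 10), the detectable difference rises by about 1%: (2.228 + 0.879)/(2.201 + 0.876) = 1.01.

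### The main analysis is an unadjusted t-test on six-month HADS that in practice rests on about 800 of 1,000 patients and leaves baseline and earlier scores unused

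*Protocol article*

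**What the plan says.** All places are in the protocol article.

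- **Statistical analysis**, main comparison: "The main analysis will compare HADS scores of all patients at t4 in arm one versus arm two using t-tests". The same paragraph adds: "The analyses will be done as according to the intention to treat principle".
- **Statistical analysis**, follow-on model: because the departments are few, certain variables will subsequently be "adjusted for in a mixed-model analysis: sex, age, stage of disease and baseline distress". This model comes after the t-test. It is described as covariate adjustment, with no mention of repeated measures.
- **Sample size**: after refusals, "this leaves about 1,000 patients participating at baseline". On later loss: "we assumed that 20% of the patients would drop out during the follow-up period due to death or withdrawal from the study". The section gives the resulting number as "leaving 800 patients at t4". The detectable difference is worked out for 400 per arm.
- **Data collection**: patients are interviewed at admission (t1), at the end of the stay (t2), and at three (t3) and six months (t4) after baseline. HADS is the primary instrument, but the text does not list which instrument is given at which visit.

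**The concern.** A t-test on t4 scores can use only patients who have a t4 score, unless scores are imputed first, and the article mentions no imputation. One patient in five is expected to have none. The plan gives the headline role to the method that makes least use of what is known about those patients. It gives a secondary role to the model that conditions on stage and baseline distress, two likely drivers of loss.

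Informative loss is plausible on the article's own account. The section on confounding and bias says that highly distressed patients refuse participation more often than others, and distress is the outcome. That observation concerns entry, not later dropout, but it makes it hard to assume that later loss is unrelated to HADS. The intervention acts on distress and cannot be blinded, so loss could also differ between arms. The described safeguard compares participants with non-participants at entry and does not address those lost afterwards. What is at stake is bias in the main treatment estimate.

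**Working it through.** **Inputs from the article (Sample size):** about 1,000 at baseline; 20% lost by t4; 800 left, 400 per arm; HADS mean 13, SD 7; 13 clusters; between-cluster coefficient k = 0.2; stated detectable difference 5.5 (4.1 if k = 0.1).

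**Not in the article, so assumed:** dropout by arm, and the gap g between the mean t4 HADS that lost patients would have had and that of completers.

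**Step 1, the plan's own figure.** 1,000 × (1 − 0.20) = 800 = 2 × 400. This reproduces exactly. About 1,000 − 800 = 200 patients have no t4 score.

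**Step 2, bias of a completer comparison.** Let d be the share lost in an arm. The full-cohort mean equals the completer mean plus d × g. With I for intervention and C for control:

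completer difference (I − C) minus full-cohort difference = −(d_I × g_I − d_C × g_C).

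The sign can go either way. If the control arm loses more distressed patients, a benefit is understated; if the intervention arm does, it is overstated.

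**Step 3, size under assumptions.**

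| Assumption | Absolute shift, HADS points |
|---|---|
| Same dropout and same gap in both arms | 0 |
| Dropout differs by 5 percentage points, gap 3 in both arms | 0.05 × 3 = 0.15 |
| Dropout differs by 10 percentage points, gap 6 in both arms | 0.10 × 6 = 0.60 |
| 20% lost in both arms, gap differs by 3 | 0.20 × 3 = 0.60 |
| 20% lost in both arms, gap differs by 7 (one SD) | 0.20 × 7 = 1.40 |

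The last row is an extreme case. All rows treat every lost patient as having a t4 score that was merely not observed. Deaths have none, and their share of the 20% is not given.

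**Step 4, scale.** 0.6 / 5.5 = 11% of the stated detectable difference, and 0.6 / 7 = 0.09 SD. The standard error ignoring clustering is 7 × √(2/400) = 0.495, so 0.6 is slightly more than one such standard error. With wards as clusters the true standard error is larger, and the bias is smaller relative to it.

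**Step 5, bias rather than power.** With k = 0.2 and mean 13 in both arms, the between-ward variance term is 0.04 × (169 + 169) = 13.52. The within-ward term is 98 / 61.5 = 1.59 with 800 patients (800 / 13 = 61.5 per ward) and 98 / 76.9 = 1.27 with 1,000. The detectable difference changes by a factor of √(15.11 / 14.79) = 1.01. Losing 200 patients costs about 1% in precision; the concern is who is lost, not how many.

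**The case against.** Four objections carry weight.

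- **The intention-to-treat label.** A reader might infer that the plan contradicts itself here. It does not in the narrow sense: analysis by allocated arm is compatible with everything stated. The mention of all patients is most naturally a contrast with the next sentence, which restricts to those highly distressed at baseline; it does not claim that everyone enrolled will have a t4 score. What stands is only that the label should not be taken to mean that all 1,000 are analysed.
- **The missing-data method may be in an analysis plan that is not shown.** This is fair, and its absence from a condensed article is not the point made here. A t-test could be run on imputed data, and powering on 800 is an ordinary dropout allowance. But the article does fix the primary test as unadjusted, and places the better-suited model second.
- **Electronic capture.** The Data collection section says: "Electronic data capture ensures that no missing data are in the data set unless the patient quits the study". A reader might infer that this is wrong for t4, because tablets are described only for t1 and t2. The documents do not support that. The sentence itself exempts patients who quit, and the capture software is introduced after the t3 and t4 modes without limitation to t1 and t2. At most, it does not cover optional paper forms.
- **The bias figures are assumptions and can be zero.** This is true, and it limits how strongly the point can be put. It does not remove the case for using data that bear on the loss.

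**Conclusion.** The point holds as a matter of analysis choice, not as a contradiction in the plan. As written, the main comparison would rest on about 800 of 1,000 patients and ignore baseline HADS and any earlier follow-up HADS, which leaves it open to bias from distress-related loss. That bias cannot be sized from the article. The range of 0.15 to 0.6 points assumes either a gap of 3 to 6 points with dropout differing by 5 to 10 percentage points, or equal 20% dropout with a gap differing by 3 points between arms. This is small beside the stated 5.5 but not negligible for an estimate that could be better protected at little cost. The change is worth making; the trial does not fail without it.

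**What to change.** 1. Make the mixed model already planned the primary analysis, with baseline HADS as a covariate and a ward random effect. This alone still uses only patients with a t4 score, but it removes bias from loss that is explained by the covariates.
2. Where HADS is collected at t2 and t3, include these as repeated outcomes with arm-by-time effects and a patient random effect, and take the t4 arm contrast as the primary estimate. Patients lost after t2 or t3 then contribute. The article implies but does not state that HADS is given at those visits, so this must be confirmed.
3. State how deaths are treated. They have no t4 HADS, and the repeated-measures model would otherwise extrapolate one silently.
4. Report deaths and withdrawals by arm, and add one delta-adjusted sensitivity analysis.
5. Say that intention to treat means analysis by allocated arm, and define the set of patients analysed.

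**Cost:** wording in the plan and some extra analysis, with no new visits. The Trial status section describes enrolment as still open. The estimate would rely on missing-at-random, which fails if loss depends on distress that was never observed, and patients with no follow-up HADS would still contribute nothing.
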